## Abstract

**Background:**

Recently factors in the relationship between gut microbiota, obesity, diabetes and the metabolic syndrome have been suggested in the development and progression of nonalcoholic steatohepatitis (NASH). In this sense, this work aims to evaluate the effects of probiotic supplementation on intestinal microbiota modulation, degree of hepatic steatosis and fibrosis, inflammation, gut permeability, and body composition.

**Methods:**

This double-blind, randomized clinical trial will include adult outpatients with a diagnosis of NASH confirmed by biopsy with or without transient elastography. All patients will undergo a complete anamnesis to investigate their alcohol consumption, previous history, medications, nutritional assessment (dietary intake and body composition), sarcopenia, physical activity level and physical and functional capacity, cardiovascular risk, biochemical parameters for assessment of inflammatory status, lipid profile, hepatic function, gut permeability, and assessment of microbiota. These procedures will be performed at baseline and repeated after 24 weeks (at the end of the study). Through the process of randomization, patients will be allocated to receive treatment A or treatment B. Both patients and researchers involved will be blinded (double-blind study). The intervention consists of treatment with a probiotic mix (*Lactobacillus acidophillus* + *Bifidobacterium lactis* + *Lactobacillus rhamnosus* + *Lactobacillus paracasei*, 1 x 10^9^ CFU for each) and the placebo which is identical in all its characteristics and packaging. Patients will be instructed to consume two sachets/day during 24 weeks and to report any symptoms or side effects related to the use of the sachets. Adherence control will be carried out through the patient’s notes on a form provided, and also by checking the number of sachets used.

**Discussion:**

The final results of study will be analyzed and disseminated in 2020.

**Trial registration:**

ClinicalTrials.gov, ID: NCT03467282. Registered on 15 March 2018.

**Electronic supplementary material:**

The online version of this article (10.1186/s13063-019-3679-7) contains supplementary material, which is available to authorized users.

## Background

According to the American Association for the Study of Liver Diseases, non-alcoholic fatty-liver disease (NAFLD) is defined as the presence of steatosis, confirmed by imaging or histology, and not caused by significant alcohol consumption, long-term use of a steatogenic medication, or a monogenic hereditary disorder. Histologically, NAFLD can be categorized into nonalcoholic fatty liver (NAFL) or non-alcoholic steatohepatitis (NASH), defined as the presence of ≥ 5% of steatosis and inflammation with hepatocyte injury, with or without fibrosis [1]. By being highly associated with metabolic comorbidities, such as obesity, diabetes mellitus, and dyslipidemia, NAFLD is considered a hepatic manifestation of the metabolic syndrome [2, 3].

The global prevalence of NAFLD diagnosed by imaging is estimated at around 25% [4]. This liver disease is positively related to the epidemic of obesity, and metabolic diseases. When NASH is diagnosed via liver biopsy, a procedure not always feasible in the studies, the estimated prevalence in the general population varies from between 1.5 and 6.4%. Patients with NASH with a higher degree of fibrosis and concurrent metabolic diseases, such as diabetes, hypertension, visceral obesity, and dyslipidemia, present a higher mortality risk. Therefore, patients with this profile have a greater requirement for treatment [1].

The gut microbiota seems to be related to NAFLD/NASH by contributing to intestinal permeability and choline-metabolism disturbance, endogenous-alcohol production, inflammatory cytokine release, and hepatic Toll-like receptor (TLR) regulation. Moreover, some studies have suggested that patients with NASH have a different microbiota composition than patients without the disease [5].

Microbiota dysbiosis is related to dysfunction of the intestinal barrier, increasing its permeability and exposing the liver to microbial translocation [6, 7]. The increased permeability allows the passage of products from the gut microbiota into the portal circulation, stimulating an inflammatory cascade and favoring the development of NASH, hepatic fibrosis, and hepatocellular carcinoma [8–10]. The relation of the intestine-liver axis in an environment of increased intestinal permeability seems to play an important role in the pathogenic mechanism of NASH. Several studies have documented the progression of NASH related to increased intestinal permeability [6, 8, 11–14].

Also, it has been described that the gut microbiota is related to liver steatosis and inflammation involving TLR, especially TLR-4, and proinflammatory cytokines [15]. Experimental studies lead us to believe that probiotics could be considered a therapeutic option in NAFLD. In our group, the effect of the probiotic *Lactobacillus rhamnosus* GG (LGG) on a model of alcohol steatosis in zebrafish was evaluated. A reduction of serum triglycerides, cholesterol, and hepatic steatosis levels was observed in treated animals [16]. There are already clinical trials that demonstrate the benefit of probiotic supplementation by reducing liver enzyme levels, steatosis severity (measured by the Fatty Liver Index), and proinflammatory cytokines, such as tumor necrosis factor alpha (TNFɑ) and interleukin (IL)-6, and also improve the lipid profile [17–21]. However, these studies are very heterogeneous in terms of the intervention time and the strains of bacteria involved.

Another concern in NAFLD is the relationship with sarcopenia [22–24], characterized by the loss of skeletal muscle mass, muscle strength and physical performance, with adverse risks [25]. Lee et al. [24] highlight that individuals with sarcopenia have a higher risk of NAFLD and liver fibrosis development. Wijarnpreecha et al. [26] and Bindels et al. [27] suggest a relationship between muscle loss and changes in gut microbiota. The authors suggest that the modulated microbiota may act on muscle physiology through amino-acid changes, influencing metabolites, such as bile acids, and modulate the production of proinflammatory cytokines, an effect correlated with an improvement in the markers of skeletal-muscle atrophy.

Currently, there is no broad-spectrum drug to treat NASH, so, to prevent or delay the progression of liver disease, the associated comorbidities must be treated separately. However, we believe that modulating the microbiota through probiotic supplementation could confer benefit on NASH, especially by reducing inflammation, and thus becoming an adjunct therapeutic option. In this context, we have designed a randomized clinical trial in order to evaluate the effect of probiotic supplementation on microbiota and in the course of NASH.

## Methods

### Study setting

This is a single-center, randomized, double-blind, placebo-controlled clinical trial that will include adult subjects with NASH treated at an outpatient clinic of the Nutrition and Dietetic Division of Hospital de Clínicas de Porto Alegre, Brazil. The present protocol was written in accordance with Standard Protocol Items: Recommendations for Interventional Trials (SPIRIT) guidelines and completing the SPIRIT Checklist [28] (Additional file 1).

### Eligibility criteria

Inclusion criteria: adult subjects diagnosed with NASH, with or without fibrosis, by liver biopsy.

Exclusion criteria: patients with human immunodeficiency virus, hepatitis B virus or hepatitis C virus infection; a significant intake of alcohol; cirrhosis; pregnancy; liver transplantation; supplements and foods with probiotics; use of immunosuppressant, antibiotic, and corticosteroid drugs, and valproic acid and amiodarone, and with any other chronic inflammatory diseases.

### Interventions

The patients will be randomized to an intervention group (probiotic) or a control group (placebo). Patients allocated to the intervention group will receive probiotic supplementation which consists of a 1-g sachet containing *Lactobacillus acidophilus* SD5221 (1 x 10^9^ CFU) + *Lactobacillus rhamnosus* SD5675 (1 x 10^9^ CFU) + *Lactobacillus paracasei* SD5275 (1 x 10^9^ CFU) + *Bifidobacterium lactis* SD5674 (1 x 10^9^ CFU), while those allocated to the control group will receive a 1-g sachet with an identical appearance (physical and organoleptic) containing polydextrose/maltodextrin as the placebo. Patients will be instructed to ingest two sachets daily with water at room temperature for a period of 24 weeks.

The patients will receive a spreadsheet to mark the intake of the sachets and write down any symptoms that may appear during the intervention period. Every 45 days, patients will be seen and adherence to treatment will be evaluated through the spreadsheet and by counting the sachets that were not consumed.

The participants will be instructed to advise the research team about the need to use any other non-routine medications, as some medications may alter the intestinal microbiota, and also to inform the team when they use a product that contains probiotics.

### Randomization

The randomization will be performed through a simple, sequential, randomization plan generated online (using the randomization.com website).

### Outcomes

Primary outcome:
Modification in fibrosis level by elastography scores

Secondary outcomes:
Gut microbiota diversity assessed by metagenomic analysisIntestinal permeability assessed by claudin-3 and lipopolysaccharide (LPS) levelsInflammatory response evaluated by *TLR-4* gene expression and biomarker cytokeratin 18 (CK-18) and C-reactive protein (CRP) levelsComponents of the metabolic syndrome evaluated by anthropometry and laboratorial assessmentModifications in the parameters of sarcopenia evaluated by Dual-energy X-ray Absorptiometry (DEXA), bioelectrical impedance analysis (BIA), physical capacity, and myostatin, a negative regulator of muscle growth, and testosterone levels

### Participant timeline

The participant timeline is presented in Fig. 1.

**Fig. 1 Fig1:**
[figure not shown]
Schedule of enrollment, interventions, and assessments

### Sample size

The sample size estimation was carried out in WINPEPI 11.20 (Brixton Health, Israel), based on data from Eslamparast et al. [29] that found a mean reduction in fibrosis score of 9.36 ± 1.9 to 6.38 ± 1.5 in NAFLD patients taking symbiotic supplementation (*P* < 0.001, compared to placebo). Thus, considering a power of 90% and a significance of 5%, adding 10% to compensate for eventual losses, it will be necessary to include 46 patients with NAFLD in the present study.

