### Statistical analysis

For the quantitative variables, the comparison between the values obtained before and after the intervention will be performed by the *t* test for parametric samples (or Wilcoxon’s signed-rank test if the data do not satisfy the assumptions for this test); for the qualitative variables, the McNemar test will be used.

In the comparison of treatments for the quantitative variables, a delta value will be computed (value before − value after); the delta values will be compared between interventions using the *t* test for independent samples (or the Mann-Whitney *U* test). Delta values can be adjusted by age and other covariates by analysis of covariance. It will be considered statistically significant if *P* < 0.05. Statistical analysis will be performed in SPSS 18.0.

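### The stated 46 patients for 90% power do not follow from the printed inputs, which are one arm's before-after change and not the between-arm difference in change that will be tested

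*Protocol article*

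**What the plan says.** The Sample size section takes its effect from one earlier study, which "found a mean reduction in fibrosis score of 9.36 ± 1.9 to 6.38 ± 1.5 in NAFLD patients taking symbiotic supplementation". Placebo enters only through a P value below 0.001, described as "compared to placebo". With 90% power and 5% significance, the section then draws its conclusion: "adding 10% to compensate for eventual losses, it will be necessary to include 46 patients with NAFLD in the present study". The Allocation section numbers patients from 1 to 46 across groups A and B, so 46 is the total over both arms.

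For the treatment comparison, the Statistical analysis section defines a delta (value before minus value after) and says that "the delta values will be compared between interventions using the" independent-samples t test, or the Mann-Whitney test. The primary outcome is the change in fibrosis level by elastography.

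**The concern.** There are two linked problems.

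First, the section presents 46 as the consequence of the figures it prints, and those figures do not lead to 46.

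Second, the figures describe the wrong quantity. A fall from 9.36 to 6.38 is the change within one arm. The planned test compares the change in one arm with the change in the other. Its power depends on the difference between the two changes and on the SD of the change. The section gives the SDs of the before and after values, but not the SD of the change, and says nothing about how far placebo patients fell.

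At stake is how the primary result will be read. If it is null, readers will set it against a claim of 90% power. The article gives them no way to see which between-arm difference that power refers to.

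**Working it through.** **Inputs from the article.** Before 9.36 (SD 1.9), after 6.38 (SD 1.5), power 90%, significance 5%, losses 10%, total 46 in two arms.

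**Assumptions, because the article does not state them.** Two-sided test; 1:1 allocation; losses handled as N/0.9, or as N × 1.1 where noted. Sample sizes use the t test with the noncentral t distribution. The normal approximation is n per arm = 2(1.960 + 1.282)² × SD²/difference².

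**Step 1. Trying to reproduce 46 with the printed fall used as a two-arm difference.** The difference is 9.36 − 6.38 = 2.98.

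| SD used | n per arm, normal approximation | n per arm, t test | Total from t test, N/0.9 |
|---|---|---|---|
| 1.5 | 6 | 7 | 14/0.9, so 16 |
| 1.71, i.e. √[(1.9² + 1.5²)/2] | 7 | 9 | 18/0.9 = 20 |
| 1.9 | 9 | 10 | 20/0.9, so 23 |

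One-sided t tests give 14 to 18. None is near 46.

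**Step 2. The planned contrast, with placebo change set to zero.** The SD of the change is √(1.9² + 1.5² − 2r × 1.9 × 1.5), where r is the before-after correlation.

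| r | SD of change | n per arm | Total with losses |
|---|---|---|---|
| 0 | 2.42 | 15 | 30 × 1.1 = 33, or 30/0.9, so 34 |
| 0.5 | 1.73 | 9 | 20 |
| 0.8 | 1.14 | 5 | 11 or 12 |

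A paired test within one arm needs 10 patients at r = 0 and 6 at r = 0.5.

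**Step 3. Working back from 46.** 46 × 0.9 = 41.4 and 46/1.1 = 41.8, so about 42 evaluable patients, or 21 per arm. With 21 per arm, 90% power corresponds to 1.03 SD and 80% to 0.89 SD. For a difference of 2.98 to equal 1.025 SD (unrounded), the SD of the change would have to be 2.98/1.025 = 2.91. With the printed SDs, that needs r = (1.9² + 1.5² − 2.91²)/(2 × 1.9 × 1.5), about −0.46. A negative correlation of that size between two measurements in the same patients is implausible.

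**Step 4. Power of 21 per arm if the printed inputs are taken literally.** For a difference of 2.98, power is over 99% with SD 1.71 or 1.9, and 97% with SD 2.42. It is not 90%.

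**Step 5. Power of 21 per arm if placebo patients also fall.** The placebo falls below are assumptions; the article gives none.

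| Assumed placebo fall | Between-arm difference | Power, r = 0 | Power, r = 0.5 | Power, r = 0.8 |
|---|---|---|---|---|
| 0 | 2.98 | 97% | >99% | >99% |
| 1.0 | 1.98 | 73% | 95% | >99% |
| 1.5 | 1.48 | 49% | 77% | 98% |
| 2.0 | 0.98 | 25% | 43% | 78% |

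The result is governed by two quantities that are not printed.

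**The case against.** The strongest reply is that 46 may be correct for inputs that were used but not printed. The cited study had a placebo comparison, and its placebo data could have been entered in the software. With the printed SDs, r = 0.5 and a placebo fall of 1.2, the test needs 21 per arm, and 42 × 1.1 = 46.2. The full protocol may record such inputs. This stands as far as it goes: 46 has not been shown to be the wrong number. It does not rescue the paragraph, which prints a one-arm change and presents 46 as what follows from it.

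A second reply is that the mismatch runs in the safe direction, because 46 exceeds what the printed inputs require. That is also right. A reader might infer from the flawed derivation that the trial is underpowered. The article does not support this: power falls below 90% only under an assumed placebo change, and no placebo change is given.

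A reader might also infer that a fall of about 3 units is out of reach here, since the trial enrols "adult subjects diagnosed with NASH, with or without fibrosis, by liver biopsy". The article gives no baseline stiffness, no distribution of fibrosis, no floor for the measure and no units for the cited score, so this cannot be concluded. Likewise, sizing for NAFLD while enrolling NASH is loose wording and not an error of substance, because the Background treats NASH as a category of NAFLD.

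Finally, the planned comparison itself is unaffected. The between-arm test of deltas remains valid whatever the sizing paragraph says.

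**Conclusion.** The paragraph is wrong as written. The printed inputs give about 16 to 23 patients in total, or at most 33 to 34 with no placebo change and no before-after correlation, against a stated 46. Read literally, they imply 97% to over 99% power with about 42 evaluable patients, not 90%. More importantly, they do not describe the contrast to be tested, so 90% power for that contrast is neither established nor refuted.

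These figures rest on a two-sided 5% test, equal allocation and the SDs of 1.9 and 1.5. The figures for the SD of the change also rest on an assumed correlation, and those in Step 5 on an assumed placebo fall as well.

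**What to change.** Keep 46 and restate the Sample size paragraph in one of two ways.

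- **Preferred:** report the between-arm difference in change and the SD of the change that were actually entered in the software, with sidedness, allocation ratio and test, and the N or power that results.
- **If those inputs cannot be recovered:** replace the claim with a statement such as: about 42 evaluable patients (21 per arm) give 90% power for a between-arm difference in change of about 1.03 SD, and 80% for about 0.89 SD, two-sided 5%.

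Either way, do not present the one-arm fall of 2.98 as the detectable treatment effect. Label any translation into score units as resting on an assumed unit and an assumed before-after correlation. NASH could replace NAFLD in the same sentence as a matter of wording.

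The cost is one paragraph. No patients are added and no analysis changes, which suits a trial in which, according to the Trial status section, forty-five patients had already started. The price is that the power statement becomes conditional.

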### Recruitment

Potentially eligible patients will be identified in the everyday clinical practice of the research staff, or referred to them for assessment of eligibility having been identified by clinical staff who are not research staff. Medical records will be checked to identify any other potentially eligible patients. The patient’s eligibility will be confirmed by the responsible researcher. After confirmation, any patient who agrees to participate in the research must sign the inform consent to begin participation.

### Allocation

Patients will be allocated to group A or group B, in a numerical sequence from 1 to 46 generated using the randomization.com website. The list will be in the possession of the researchers responsible for recruitment, but only the external investigator will have access to which patients are receiving probiotic or placebo. Delivery of the supplementation will be made to the participants according to the list generated by researchers and will be communicated to the external researcher in the sequence on the list. The products are stored in boxes identified according to the researchers’ randomization list. The allocation sequence was generated, and will be administered, by the external researcher and the participants will be included and referred to the procedures by the other researchers.

### Blinding

Patients and the researchers administering the study will not know the composition of each sachet of supplements and the participant’s allocation treatment. An external researcher will be unblinded. Researchers will know which supplements each participant received only at the end of the study. The external researcher will be informed about the composition of each supplement if needed.

### Data collection methods

The evaluations will be carried out by three trained researchers: two registered nutritionist dietitians and one undergraduate student.

#### Clinical evaluation

The data collection protocol includes demographic data, clinical diagnosis and diagnostic methods, medications in use, alcohol consumption, smoking status, and blood pressure measurement. In addition, details of the disease diagnosis (liver biopsy and transient elastography) are recorded.

#### Diagnosis

The patients were, or will be, diagnosed with NASH by liver biopsy, which is the gold standard procedure. Biopsies were, or will be, performed at Hospital de Clínicas de Porto Alegre (HCPA) or another institution, requested in the outpatient clinic as needed and medically indicated. The procedure is invasive and requires some care, but the recovery is fast. A fragment of liver is removed for analysis and used for classification as not NAFLD (< 5% of hepatic steatosis), NAFL (≥ 5% of hepatic steatosis without evidence of hepatocellular injury in the form of hepatocyte ballooning), and NASH (≥ 5% of hepatic steatosis and inflammation with hepatocyte injury, with or without any fibrosis). Liver biopsy results are also scored by the NAFLD Activity Score (NAS), which is a tool for measuring change in liver histology [1].

#### Hepatic structure and funcional assessment

Liver fibrosis will be assessed by transient elastography (FibroScan). The Controlled Attenuation Parameter (CAP) is a tool based on the FibroScan, used for the detection and quantification of liver steatosis. The elastic wave propagates through the liver at a certain rate dependent on hepatic stiffness (fibrosis). The higher the velocity, the greater the stiffness, measured in kilopascals (kPa), and the greater the extent of the fibrosis. The median is considered the most representative value, being the immediate result, and is numerical and expressed in kPa [30].

In addition, blood samples will be collected for the evaluation of the genetic expression of biomarker *TRL4*, and CK-18, which are directly associated to liver inflammation.

#### Scores

The NAFLD Fibrosis Score, APRI Score and Fatty Liver Index [31–33] are useful tools for the diagnosis and monitoring of patients with NAFLD. The NAFLD Fibrosis Score is based on the following parameters: age, Body Mass Index (BMI), whether type-2 diabetes mellitus or impaired fasting glucose, alanine aminotransferase, aspartate aminotransferase, and platelet and albumin levels, while the APRI Score includes the aspartate aminotransferase level and platelet count. The Fatty Liver Index diagnoses fatty liver using laboratory parameters (alanine aminotransferase, aspartate aminotransferase, gamma glutamyl transferase, glucose, insulin, triglycerides, cholesterol levels), and clinical (gender, age, alcohol intake) and anthropometric (waist circumference, triceps, biceps, subscapular and supra-iliac skinfolds) findings. The scores will be calculated via an online calculator (MDCalc.com).

#### Microbiota assessment

For the microbiota assessment, the patients will be instructed to collect a stool sample within 24 h prior to their next visit (baseline and close-out) using a disposable pad and sterile paddle pot. Samples will be immediately frozen in the patient’s own freezer. On the day of the consultation, the patient will transport the sample to the research center using cooling elements and a styrofoam box. Afterwards, samples will be stored at − 80 °C until analysis.

For intestinal microbiota assessment, the bacterial deoxyribonucleic acid (DNA) will be extracted from the feces using the QIAmp DNA Stool Mini kit (Qiagen, São Paulo, Brazil). Extracted DNA will be kept at − 20 °C until the moment of use. Approximately 50 ng DNA will be used for amplification of the V4 hypervariable region of the bacterial *16S* rRNA gene by polymerase chain reaction (PCR). The resulting product will be purified and used in the preparation of the emulsion PCR, followed by the sequencing reaction in the Ion Torrent Personal Genome Machine (Life Technologies, São Paulo, Brazil). The sequencing data will be processed using QIIAME software. Bacterial-diversity analyses will be based on the degree of similarity between *16S* rRNA sequences which are grouped into Operational Taxonomic Units (OTUs). Sequencing and analysis will be performed at the HCPA Protein Analysis Unit (UAMP).

